### Primary Outcome

Our primary outcome is the number of minutes of moderate-and strenuous physical activity per week as measured by an adapted version of the Leisure Time Exercise Questionnaire [32]. In this questionnaire, participants are asked to report the average weekly frequency and duration with which they engaged in strenuous, moderate, and light exercise over the past month. Consistent with a change made to the questionnaire in a study of colorectal cancer survivors [33], participants were asked to report the average duration of time they spent exercising at each intensity, in addition to the frequency. In addition, some of the physical activities were deleted from the instrument, because they were not common activities in Australia (e.g., horseshoes, snowmobiling). The validity and reliability of the Leisure Time Exercise Questionnaire compares favourably with other physical activity questionnaires [34].

### Secondary Outcome

The secondary outcome is the impact of the physical activity program on the psychological well-being, quality of life, and objective physical functioning of prostate cancer survivors.

### Quality of life

Quality of life will be measured using a cancer-specific instrument: the European Organization for Research and Treatment of Cancer core quality of life questionnaire (EORTC QLQ-C30, version 3 [35]) and the prostate tumour-specific module (EORTC QLQ-PR25 [36]). The EORTC QLQ-C30 comprises both multi-item subscales and single items, including five functional subscales, three symptom subscales, a global health status subscale, and six single items. The EORTC QLQ-PR25 is a 25-item questionnaire designed for use among patients with localised prostate cancer, which has four subscales: urinary symptoms, bowel symptoms, treatment-related symptoms, and sexual functioning. The EORTC QLQ-C30 has convergent and discriminant validity, is responsive to change over time, and has adequate internal consistency reliability [35]. The EORTC QLQ-PR25 also has convergent and discriminant validity, and has adequate internal consistency reliability [36].

### Anxiety

Anxiety related to prostate cancer will be measured with the Memorial Anxiety Scale for Prostate Cancer (MAX-PC) [37]. This instrument has 18 items that represent three subscales: prostate cancer anxiety, prostate specific antigen anxiety, and fear of recurrence. The scale has concurrent validity with established anxiety measures (e.g., the anxiety subscale of the Hospital Anxiety and Depression Scale [38]) and discriminant validity, as well as sound internal consistency and test-retest reliability [37,39]. The MAX-PC appears to be a more sensitive measure of cancer-related changes in anxiety than comparable measures [39].

### Depression

Symptoms of depression will be assessed using the Centre for Epidemiological Studies Depression Inventory (CES-D) [40]. This instrument has 20 items representing symptoms associated with depression. The scale has strong concurrent validity, with clinical and self-report criteria, and sound construct validity [40]. The CES-D has high internal consistency and acceptable test-retest reliability. The authors of two recent reviews of depression and emotional distress measures for use with cancer patients strongly recommend the use of the CES-D as a measure of depression [41,42].

### Objective Physical Functioning

Objective physical functioning will be assessed using standard measures: resting heart rate, blood pressure, limb girth circumferences, 6 minute walk, sit to stand (30 seconds), 1 repetition maximum strength test, and Apley's shoulder test [43]. These standard tests are simple, non-invasive, can be conducted with minimal equipment and space, and have been validated for use with older people and chronic disease groups [43].

### Accelerometer Measures

Accelerometers will be worn by participants to quantify physical activity objectively. The Actigraph GT3X accelerometer is a small matchbox-sized unit worn on a belt on the hip that is a valid and reliable tool for measuring physical activity among adults [44,45], and will be worn for seven consecutive days. Movement count thresholds based on established thresholds [45] will be used to calculate the average time participants spent in moderate-to vigorous-intensity physical activity. A specially designed macro will be used to manage the data and for examining physical activity outside of work hours for employed individuals (data are recorded in 'real time' and are extractable for user-specified time periods). The whole day will also be analysed to examine potential compensation as a result of engaging in the physical activity program.

All study participants will be asked to wear an accelerometer for two 7-day periods. For participants in the intervention condition, this will be in the week between their fitness assessment session and commencement of the 12 week physical activity program, and the week following completion of the exercise program (week 13). For participants in the control condition, the two time periods will be equivalent.

Participants will be asked to wear the accelerometer on a belt around their waist over their right hip for a seven day period, except when they are sleeping, bathing, or swimming. Accelerometers will be initialized to begin data collection at 5:00 am the day after they are received by participants (giving seven complete days of recorded activity), and the epoch of integration is set at 30 seconds. As the monitor records even slight motion as a nonzero count, a sustained 20-minute period of zero counts is considered a non-wearing period, and missing data will be imputed using the Expectation Maximization (EM) algorithm as described previously [46].

Participants who are unable to provide at least three days with a minimum of six hours of data will be excluded from this analysis as the accuracy of imputation is too imprecise. Accelerometer counts will be summarised into time spent in each of four activity intensities with thresholds for sedentary, light, moderate, and vigorous activity intensity ranges of < 100, 101-1951, 1952-5724, ≥ 5725 counts min^-1 ^respectively [45]. In addition, counts ≥ 1952/min will be converted to their metabolic equivalent (MET; multiples of resting metabolic rate in kcal kg h-1) and summed to create the total "intensity weighted" minutes (i.e., MET-minutes) of Moderate-Vigorous Physical Activity (MVPA) [45,46]

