### Physical Activity Program

Participants will initially undertake a one-on-one session with the exercise physiologist, which will involve a discussion of each participant's beliefs in his or her ability to be physically active, physical activity preferences, outcome expectations, goals, and strategies for using facilitators and overcoming barriers to performing physical activity. The topics for this discussion are based on the concepts (previously identified) within social cognitive theory that are particularly relevant to health behaviour [19,20]. This is to increase long-term adherence to physical activity.

Emphasis will be placed on exercise physiologists regularly counselling participants throughout the structured physical activity sessions. The counselling topics will be based on the constructs of social cognitive theory. Exercise physiologists involved in this study will be trained in the application of social cognitive theory to physical activity uptake and adherence for survivors of prostate cancer. Exercise physiologists will be provided with checklists to ensure that they are regularly discussing key factors, including setting goals, aligning activity with outcome expectations, overcoming barriers and drawing on facilitators.

Based on previous work with prostate cancer patients [25], participants will undertake a 12-week program that will include supervised physical activity sessions and unsupervised physical activity. During the supervised sessions, several participants may be exercising at the same time. As participants will enter and leave the program at varying times and will have different weekly schedules, no attempt will be made to allocate participants to groups that will train in 12-week blocks. The physical activity program will be tailored to suit the ability of each participant. Exercise physiologists will lead two supervised sessions per week and will advise participants on what physical activity to undertake during their one non-supervised session per week.

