**Secondary Outcomes**	
Objective Physical Functioning	Resting heart rate, blood pressure, limb girth circumferences, 6 minute walk, sit to stand (30 seconds), 1 repetition maximum strength test, and Apley's shoulder test [43].
Accelerometer measure	The Actigraph GT3X accelerometer is a small matchbox-sized unit worn on a belt on the hip that is a valid and reliable tool for measuring physical activity among adults [45,46], and will be worn for eight consecutive days, before the intervention commences and during the final week of the intervention.
Quality of Life	European Organization for Research and Treatment of Cancer core quality of life questionnaire (EORTC QLQ-C30, version 3 [35]) and the prostate tumour-specific module (EORTC QLQ-PR25 [36]).
Anxiety	Memorial Anxiety Scale for Prostate Cancer (MAX-PC) [37]
Depression	Centre for Epidemiological Studies Depression Inventory (CES-D) [40].

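### Compensation for the program is to be examined by accelerometry, but the methods text places the follow-up wear in week 13, after the supervised sessions have ended, while Table 1 places it in the final program week

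*Protocol article*

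**What the plan says.** The Accelerometer Measures section gives the whole-day analysis a specific purpose: "The whole day will also be analysed to examine potential compensation as a result of engaging in the physical activity program". Its next paragraph fixes the wear schedule: "All study participants will be asked to wear an accelerometer for two 7-day periods". In the intervention arm the first period falls before the 12-week program starts, and the second is "the week following completion of the exercise program (week 13"). For the comparator, "For participants in the control condition, the two time periods will be equivalent".

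Table 1, under secondary outcomes, gives a different schedule. There the device "will be worn for eight consecutive days, before the intervention commences and during the final week of the intervention".

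The section adds that "data are recorded in 'real time' and are extractable for user-specified time periods". The only time split it names is activity outside work hours in employed men. The Physical Activity Program section states that "Exercise physiologists will lead two supervised sessions per week", each of about 50 minutes, plus one unsupervised session. Afterwards each man receives an individual program aimed at maintaining 150 minutes a week.

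**The concern.** Compensation means that a man does less elsewhere because he is attending the program. It can be seen only while he is attending. The methods text states the purpose, the measure and the week, and the week does not fit the purpose. Table 1 gives a week that does fit, so the article contains two schedules, only one of which can answer the question it sets.

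At stake is whether the trial can say that the program adds activity or merely replaces it. With week-13 data, a whole-day difference near zero could be read as full compensation when it shows only that activity stopped with the sessions. A positive difference could be read as absence of compensation when it shows only that men stayed active afterwards.

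**Working it through.** The plan gives no figure on this point, so there is none to reproduce. The check sets the two schedules side by side and applies a simple identity.

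**Schedules**

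| Item | Accelerometer Measures text | Table 1 |
|---|---|---|
| Second wear period | Week 13, after the program | Final week of the intervention |
| Wear length | 7 days | 8 days |
| Supervised sessions in that week | 0 | 2 |

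**Inputs**
- Two supervised sessions a week of about 50 minutes (Physical Activity Program): S = 2 × 50 = 100 minutes.
- Share of session minutes given up elsewhere: f, assumed to be 0, 0.5 or 1.
- For simplicity, every session minute is assumed to register as activity.

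**Formulae**
- Displaced minutes: C = f × S.
- Whole-day difference from control: S − C.
- Difference outside supervised sessions: −C.

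**Results (minutes a week)**

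| Week | f | Whole day | Outside sessions |
|---|---|---|---|
| Program running, S = 100 | 0 | 100 − 0 = +100 | 0 |
| | 0.5 | 100 − 50 = +50 | −50 |
| | 1 | 100 − 100 = 0 | −100 |
| Week 13, S = 0 | any | 0 | 0 |

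In a program week both quantities move with f. In week 13 neither does, so no choice of time window recovers displacement by the supervised sessions.

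**Reading a null in week 13.** Let M be the extra activity a man does under his individual follow-on program, and D what he gives up to do it. The whole-day difference is M − D. It is zero if M = D = 0 (activity not maintained) and also if M = D > 0 (maintained but fully offset). The total alone cannot separate the two.

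**Sensitivity of the dose.** The program content gives 20 aerobic minutes per session; the rest is resistance, balance and flexibility work. The article does not say how much of that would pass the moderate-intensity count threshold. If only aerobic time registered, S = 2 × 20 = 40 and the program-week whole-day values would be +40, +20 and 0. The sizes change; the contrast between the two weeks does not.

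**Why no power figure is given as the magnitude.** With 220 × 0.9 / 2 = 99 men per arm and an SD of 126.6 minutes, the standard error is 126.6 × √(2/99) = 17.99. Ignoring clustering, a displacement of 50 minutes gives z = 50 / 17.99 = 2.78 and power of about 79%. A displacement of 20 minutes gives z = 1.11 and about 20%. The SD comes from weekly activity minutes in another project, not from accelerometry, and the dose is assumed, so the answer is set mainly by the assumptions.

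**The case against.** A reader might infer something stronger: that a whole-day total adds program and other activity together and therefore hides compensation in whichever week the device is worn. The documents do not support that.

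- In a program week the total, compared with baseline and control, is a valid net measure. Full compensation brings it to about 0, and partial compensation shows as a shortfall against the dose.
- The article states no hypothesis or decision rule for this analysis. To say that it tests for no net difference, or would conclude that compensation was absent, is to supply a rule it does not contain.
- Counts are also to be summarised as sedentary and light time, where compensation could appear even if moderate and vigorous time rises.
- The exact contrasts may properly sit in a fuller analysis plan.

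All of this stands. One qualification applies: reading a shortfall needs a dose on the accelerometer scale, which the article does not give, so the total alone would struggle to tell partial compensation from a low delivered dose.

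It can also be said that Table 1 already has the right week, and that week 13 is not empty because men leave with an individual program. The first shows that the article contradicts itself, not that the methods text is sound. The second means that compensation for the follow-on activity might appear in week 13, but that is not compensation for the supervised sessions.

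Finally, this is one sentence about a secondary measure. That limits the importance of the point, not its correctness.

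**Conclusion.** The point holds in a narrow form. The methods text and Table 1 disagree on the second wear week and on wear length. Under the methods text, displacement of other activity by the supervised sessions cannot be observed, and a null whole-day difference cannot be told apart from activity not being maintained. Under Table 1 the compensation question can be answered, and the whole-day total is a legitimate net measure of it.

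The conclusion about week 13 rests only on the stated 12-week program length and the stated wear week. The minute values assume a 100-minute dose (or 40 if only aerobic time registers) and assumed shares compensated; they illustrate the logic and do not estimate an effect. The consequence is confined to interpretation of a secondary measure, so this is a minor but worthwhile correction.

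**What to change.** Reconcile Table 1 and the Accelerometer Measures text on the wear week and on seven or eight days, then take one of two routes.

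1. **Device worn while the program is running.** Keep the whole-day analysis and label it the net effect. Add a between-arm comparison that uses the time stamps to separate supervised-session time from other time. Include sedentary and light time as well as moderate and vigorous time. State that the weekly unsupervised session has no timetable and cannot be removed, so some program activity stays in the other time. State also how control men are handled. Deleting matched clock windows from their record is debatable: they have no session timetable, and the deletion would also remove activity that a session directly displaces.
2. **Wear kept in week 13 only.** Remove the compensation claim and describe the analysis as activity after the program.

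The cost is small. The second route is wording alone. The first uses a wear week already in Table 1 and data that can already be extracted by time window. Its one addition is to log the date and time of each attended session, because the Procedures section provides a timetable and a total number attended but does not say that times are kept. The first route also gives up the week-13 reading of post-program activity unless a further wear period is added.

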### Mediators

The influence of individual and environmental mediators on participation in physical activity will be determined by the following measures.

### Self-efficacy

Both task and barrier (self-regulatory) self-efficacy will be measured using the methods Bandura [19,47] has proposed. Task self-efficacy will be assessed through asking participants to rate how confident they are that they can perform three physical tasks: walking fast (light perspiration), running, fast swimming or cycling hard, and doing exercises with weights. For each task, they will be asked the confidence with which they believe they can perform these tasks for three time durations: 10, 20, and 30 minutes. Confidence will be measured on an 11-point Likert scale, which is anchored by 0 (not at all confident) and 100 (extremely confident). Similar items have been included in previous physical activity and cancer research in which task self-efficacy was measured [48].

Barrier self efficacy will be assessed through asking participants to rate how confident they are that they can perform physical activity when faced with specific barriers. The items (barriers) came from Bandura's [47] self-efficacy to regulate exercise instrument, with supplementary items from research of physical activity for prostate cancer survivors [8] and barrier self efficacy and cancer patients [48]. The 11-point Likert scale used in the measurement of task self-efficacy will also be used to assess barrier self-efficacy.

Outcomes will be measured using the Multidimensional Outcome Expectations for Exercise Scale (MOEES) [49], which was designed for older adults. The MOESS has 15 items that represent three sub-scales: physical, social, and self-evaluative outcome expectations. Participants respond to each item on a 5-point Likert scale from 1 (strongly disagree) to 5 (strongly agree). The instrument's construct validity has been demonstrated through confirmatory factor analysis and significant correlations with other constructs consistent with the predictions inherent in social cognitive theory [49,50]. The subscales of the MOEES have good internal consistency reliability (α = .81 to .84) [49].

### Goals

Goals will be measured using items adapted from previous physical activity research in which social cognitive theory constructs were assessed [51]. Participants will be asked to indicate the number of days per week they intend to perform at least 30 minutes of exercise at a light, moderate or strenuous intensity. At each questionnaire time point, participants will be asked their current goals and their goals in 12 weeks.

### Socio-structural factors

Socio-structural factors facilitating or impeding participation in physical activity will be measured using guidelines for the development of scales to assess barriers to physical activity for cancer patients [52]. The content (i.e., facilitators and impediments) of the scale was drawn from our prior work with prostate cancer survivors [8]. Participants will be asked their perceptions of the frequency with which each facilitator and barrier occurs using a 5-point Likert scale anchored by 0 (never) and 4 (always). These barriers and facilitators will be addressed by the exercise physiologists throughout the intervention.

### Procedures

Following ethical review and approval, we will invite clinicians from three healthcare settings to participate in the study. Clinicians will be randomly allocated to either the intervention or control conditions and trained prior to commencement of the study in the study's objectives and clinician requirements including the referral process, requested dialogue and documentation completion. Adherence to the intervention and control groups' processes, will be monitored weekly by the project manager.

Eligible patients will be identified by the health service oncology nurses prior to presentation to either the public health service outpatient clinic or private health service rooms for their follow up consultation. During clinic sessions, members of the research team will approach eligible patients and introduce the study to the patient, provide an information package and seek verbal approval to follow them up within 48 hours regarding their interest in participating in the study.

#### Intervention condition

During the consultation, clinicians randomised to the intervention arm will determine the patient's eligibility to be involved in the active exercise program and if eligible, provide each patient with a referral (Figure 1) to participate in the active exercise program and say *"I understand you have been given some information about a research project that is being conducted. You have been assigned to the exercise group. I recommend that you take part. The project manager will call you in a couple of days to see if you would like to take part in the study. Your decision to take part in the study will not affect your treatment or care in any way"*.

**Figure 1 F1:**
[figure not shown]
**Referral slip provided to participants by clinicians in the intervention group**.

If the clinician does not believe that the patient is suitable for the study, they do not give the referral slip to the patient, but complete a form to indicate reasons for non-suitability (eg. co-morbidities; poor health status) and say, *"I understand you have been given some information about a research project that is being conducted. Due to your current state of health, I do not recommend that you take part in this study. I will let the researchers know that you cannot participate"*.

#### Control condition

The control condition involves participants receiving usual care from their clinicians regarding physical activity and, no referral to the active exercise program. Eligible patients will be approached by a team member to discuss the project and if the patient agrees, will be given the information package for the patient to take home and consider participating the project.

Clinicians in the control group will say, *"I understand you have been given some information about a research project that is being conducted. Although you have not been assigned to the exercise group, I recommend that you take part in the study. The project manager will call you in a couple of days to see if you would like to take part in the study. Your decision to take part in the study will not affect your treatment or care in any way"*.

If the clinician does not believe that the patient is suitable for the study, they complete a form to indicate reasons for non-suitability, and say the following:

*"I understand you have been given some information about a research project that is being conducted. Due to your current state of health, I do not recommend that you take part in this study. I will let the researchers know that you cannot participate"*.

To ensure the integrity of the trial's procedures, each of the clinicians and health service oncology nurses will undergo specific training and quality assurance assessments throughout the recruitment phase of the study.

Clinicians in both the intervention and control groups will discuss involvement in the project and provide a recommendation to participate if s/he considers it is feasible for the patient to participate. If the clinician determines the patient should not participate, s/he will complete the Reason for Non-Suitability Form and record the reason for non-participation, for example, pre-existing medical conditions, and the patient will be advised accordingly.

If the patient is eligible and has agreed to be followed up, the project manager will telephone them within 48 hours to determine the patient's interest in participating, answer any questions he may have and if happy to participate, request return of the signed consent form and baseline questionnaires. Once a consent form has been returned, the project manager will arrange a time for the participant's first fitness assessment. Figure 2 shows the recruitment and data collection time points for the study.

